#### Antibiotic use

The use of antibiotic therapy greater than two courses lasting more than 1 week within a year will be considered a protocol violation warranting withdrawal. Topical antibiotics are permitted.

### Early discontinuation/withdrawal/treatment failure

Patients may be withdrawn from the study if any of the following occurs:

The patient requests withdrawal from the study.Fails to attend one of the major study visits.Treatment failure, defined as:Clinical recurrence: symptoms typical of Crohn’s disease, necessitating unscheduled endoscopic or surgical intervention or addition of new drug therapy, associated with confirmed active disease.Failed corticosteroid withdrawal.Serious adverse events or complications necessitating cessation of therapy.Pregnancy.The investigator can also decide to withdraw a patient from the study if he/she considers it as necessary (eg, subsequent non-respect of inclusion criteria, a change in diagnosis).

At the time of withdrawal/discontinuation, patients will undergo a disease activity assessment including CRP, calprotectin, sonographic and endoscopic assessment if possible.

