#### Corticosteroid use

Participants can enter the study on prednisolone 20 mg or below, or budesonide 6 mg or below. However, mandatory corticosteroid tapering will be required from week 0 of 2.5 mg of prednisolone per week or 3 mg of budesonide every 2 weeks to ensure that participants do not remain on corticosteroids at the primary endpoint assessment.

Commencement of corticosteroid therapy after study entry will be considered a protocol deviation. However, patients can remain in the study unless it occurs within 4 weeks of the primary endpoint assessment, or if greater than two courses of more than 1 month duration are required during the entire study, either of which would be considered a protocol violation warranting withdrawal.

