### Statistical analysis

Primary analysis will be using modified intention-to-treat population, that is all patients who were randomised and received at least one dose of the study treatment. Per-protocol analysis will be performed as a secondary analysis.

The primary endpoint is the achievement of clinical response at week 8, defined as either a reduction in CDAI of ≥100 points or a CDAI score of <150 points. This primary outcome will be analysed using a general linear model with binomial distribution and log link, with results presented as risk ratio and 95% CIs. A two-sided p value of less than 0.05 will be considered statistically significant.

All binary secondary outcomes in both the induction and maintenance phases will be compared between arms using a general linear model with binomial distribution and log link. Time taken to achieve a clinical outcome will be compared between groups using Kaplan-Meier survival analysis and Cox regression model.

All continuous secondary outcomes will be compared between groups using analysis of covariance. Model fit will be assessed by visual inspection of the residuals, and outcomes might be transformed if required. If the transformation will not yield improved model fit, then the rank sum test will be used for comparison.

There will not be corrections for multiple comparisons, but the results will be interpreted in view of multiple comparisons.

The number of participants in the open-label phase extension is expected to be small, providing for mainly descriptive analysis. However, to gain a larger impression of the impact of active FMT versus placebo, combined active blinded and unblinded FMT outcomes compared with placebo will be assessed.

The primary aim of the open-label induction phase is to enable the majority of participants in the study to access FMT therapy.

Subgroup analyses will include outcomes in the upper and lower gut delivery cohorts, as well as many of the patient demographic variables.

No interim analyses will be performed. The missing data strategy will depend on the type of intercurrent event.

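### Withdrawal rules take dosed patients out of the study, not just off study product, so the week-8 CDAI that the primary analysis needs may never be collected

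*Protocol article*

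**What the plan says.** All of the following is in the protocol article.

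- **Early discontinuation/withdrawal/treatment failure.** One list covers all three situations, under the lead-in "Patients may be withdrawn from the study if any of the following occurs". The reasons include "Fails to attend one of the major study visits", treatment failure, failed corticosteroid withdrawal and "Serious adverse events or complications necessitating cessation of therapy". On leaving, "patients will undergo a disease activity assessment including CRP, calprotectin, sonographic and endoscopic assessment if possible".
- **Corticosteroid use.** A steroid start after entry is a deviation, but "patients can remain in the study unless it occurs within 4 weeks of the primary endpoint assessment" or unless more than two courses of over a month each are needed, "either of which would be considered a protocol violation warranting withdrawal".
- **Antibiotic use.** More than two courses of over a week each within a year "will be considered a protocol violation warranting withdrawal".
- **Statistical analysis.** The primary population is modified intention-to-treat: "all patients who were randomised and received at least one dose of the study treatment". The endpoint is CDAI-based clinical response at week 8. Missing data are to be handled according to the type of intercurrent event.
- **Table 2 (Clinical outcomes assessments).** The Safety row runs for up to 5 years after withdrawal or exit. No other row mentions patients who have left.
- **Sample size and Discussion.** 60% against 30% response, two-sided alpha 0.05, 80% power, 20% attrition in each group, 120 enrolled so that 96 complete induction.

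**The concern.** Stopping study product and leaving the study are different events, and the article treats them as one. A patient who stops therapy after an adverse event, fails the steroid taper or meets the treatment-failure definition can be removed from the study altogether. That patient stays in the primary analysis set because a dose was given, but nothing in the article keeps them in follow-up until the week-8 CDAI.

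Several of these reasons reflect lack of efficacy and others reflect harm. The resulting gaps are therefore unlikely to be random and may differ between FMT and placebo. The risk ratio would then depend partly on assumptions about patients whose outcome could have been recorded at a visit already in the schedule.

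**Working it through.** **1. Rule against need**

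| Event before week 8 | Stated consequence | Follow-up stated for that patient | Needed by the primary analysis |
|---|---|---|---|
| Treatment failure, failed steroid withdrawal, therapy stopped for a serious adverse event, missed major visit | May be withdrawn from the study | Assessment on leaving; safety surveillance | CDAI response at week 8 |
| Steroid start within 4 weeks of the primary assessment | Warrants withdrawal | As above | CDAI response at week 8 |
| Earlier steroid start | May remain | Normal schedule | Available |
| More than two long steroid courses, or more than two long antibiotic courses in a year | Warrants withdrawal | As above | Mainly affects weeks 52/60 |

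The 4-week steroid window is half of the 8-week induction. A patient entering on prednisolone 20 mg and tapering by 2.5 mg per week from week 0 needs 20 / 2.5 = 8 weeks to reach zero. A failed taper can therefore fall just before the endpoint.

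More than two steroid courses of over a month each cannot accrue within 8 weeks of study treatment. More than two antibiotic courses of over a week each are very unlikely to. That is why the last row concerns maintenance.

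**2. The plan's own sample size**

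Inputs: 30% and 60%, two-sided alpha 0.05, power 80%, allocation 2:1 (Randomisation and stratification), dropout 20%. Normal approximation with pooled variance, no continuity correction:

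- Pooled proportion = (0.30 + 2 × 0.60) / 3 = 0.50.
- n(placebo) = [1.96 × √(0.5 × 0.5 × 1.5) + 0.842 × √(0.3 × 0.7 + 0.6 × 0.4 / 2)]² / 0.30² ≈ 31.5, rounded up to 32.
- n(FMT) = 2 × 32 = 64, total 96. Power at 96 is 80.6%.
- 96 / 0.80 = 120.

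The stated 96 and 120 reproduce, so the sample size is not in dispute.

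**3. Most patients who could be affected**

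Assume all 120 are randomised and dosed, and all 20% attrition comes from these rules. Both assumptions are upper limits.

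- FMT: 80 dosed, 16 missing, 64 observed. Placebo: 40 dosed, 8 missing, 32 observed.
- Observed responders at the planned rates: 0.60 × 64 = 38.4 and 0.30 × 32 = 9.6.

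| Assumption about the missing | FMT | Placebo | Risk ratio |
|---|---|---|---|
| All non-responders | 38.4/80 = 0.48 | 9.6/40 = 0.24 | 2.00 |
| FMT all non-responders, placebo all responders | 0.48 | (9.6 + 8)/40 = 0.44 | 1.09 |
| FMT all responders, placebo all non-responders | (38.4 + 16)/80 = 0.68 | 0.24 | 2.83 |

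**4. Power, same approximation**

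- 20% lost and counted as non-responders (48% against 24%, 80 and 40 patients): 73.1%.
- 10% lost (54% against 27%): 81.7%.
- 5% lost (57% against 28.5%): 85.5%.
- All 120 followed, with 60% against 30% still holding: 88.8%.

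**5. Unequal withdrawal (illustration with assumed rates)**

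Suppose 10% of FMT and 30% of placebo patients are withdrawn, all non-responders, and the true rates are 60% and 30%. Among those remaining the rates are 0.60/0.90 = 66.7% and 0.30/0.70 = 42.9%. The risk ratio is 1.56 instead of 2.00. Counting the withdrawn as non-responders restores 2.00 here, but only because the illustration makes them so.

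**The case against.** The other side has several good points.

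- **Withdrawal is not automatic.** A reader might infer that every listed event removes the patient. The general list says only that patients may be withdrawn, and most steroid starts allow the patient to stay. What is left is a permission exercised by judgement, and a firmer rule for a steroid start close to the endpoint. Neither protects the week-8 outcome.
- **The exit assessment may include the CDAI.** A reader might infer that it is left out, because only CRP, calprotectin, sonography and endoscopy are named. The wording is a disease activity assessment that includes those items, and Table 2 measures disease activity by the CDAI. The documents do not support saying that it is excluded. They do not name it either, and the assessment takes place on leaving, not at week 8.
- **The analysis plan can handle missing data.** It can, and its absence here is no fault. It can also class treatment failures as non-responders. It cannot supply a week-8 CDAI for patients removed for an adverse event, an earlier missed visit or an investigator's decision.
- **If treatment failures are set to non-response, their later CDAI does not enter the primary result.** True. The gain for the primary analysis comes from the remaining patients, whose number the article does not give. For the failures, the later value would support a sensitivity analysis.
- **The range 1.09 to 2.83 is generic.** Agreed. Any trial of this shape with 20% missing outcomes has these bounds. The 20% includes patient-requested withdrawal and loss to follow-up, which no rewording prevents. Patients lost during the 3-week optimisation phase before randomisation never enter the analysis set. The lower bound needs every missing placebo patient to be a responder, which is implausible when many of the reasons are failures.
- **The article is condensed.** The full protocol may say more. The article's Consent section states in general terms that clinical data are gathered for 5 years, but does not mention withdrawn patients or the week-8 CDAI.

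**Conclusion.** The point holds as a flaw in a stated data-collection rule. As written, dosed patients can leave the study for reasons largely related to outcome, and nothing shown keeps them in follow-up for the week-8 CDAI on which the primary analysis judges every dosed patient. The antibiotic rule and the repeated-steroid-course rule bear mainly on weeks 52 and 60.

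The size cannot be fixed from the documents, because the part of the 20% attrition due to these rules is not given. At most 16 FMT and 8 placebo patients are affected. With all of them non-responders the risk ratio stays at 2.0, although power falls to about 73%. The values 1.09 and 2.83 mark the limits of what missing outcomes could do and forecast nothing. The documents support neither a claim that the primary result will be biased by a given amount nor a claim that the sample size is wrong.

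**What to change.** Leave every stopping criterion as it is and change only what happens to data collection afterwards:

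1. State that stopping study product does not end follow-up. Only withdrawal of consent does.
2. For every dosed patient who has not withdrawn consent, collect the CDAI at the scheduled week-8 visit, and at week 52 or 60 if the patient was re-randomised.
3. Name the CDAI in the assessment made on stopping.
4. State that patients who meet the protocol's treatment-failure definition before week 8 count as non-responders in the primary analysis, and say which items of the withdrawal list belong to that definition. Say how each other reason enters the analysis.

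The cost is an amendment to the wording and a few extra contacts, for at most about 24 induction patients on the plan's own attrition, at time points already scheduled. Recruitment began in May 2022, so new visits help only patients who have not yet passed them. For earlier patients, the number without a week-8 CDAI and the reason should be reported by arm.

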### Primary and secondary endpoints

The primary and secondary endpoints are detailed in table 1.

**Table 1 T1:** Primary and secondary endpoints

Outcome	Definition	Timepoint
Primary		
Clinical response	CDAI decrease of ≥100 or CDAI<150	Week 8
Secondary		
Clinical remission	CDAI<150	Week 8 and week 52Week 16 and week 60 (for open FMT group)
Endoscopic response	SES-CD reduction by 25% and 50%	Week 8 and 52Week 16 and 60
Endoscopic remission	SES-CD ≤2 or absence of ulcers	Week 8 and week 52Week 16 and 60
Histological remission	The absence of ulcers; the absence of acute inflammation histologically; one of either Geboes Score or Robarts Histology Index	Week 8 and 52Week 16 and 60
Radiological remission	IUS (BWT<3 mm and/or Limberg 0 or 1) or MRI (wall thickness<4 mm and no or minimal wall enhancement)	Week 8 and 52Week 16 and 60
Biochemical response	Normalisation of CRP and faecal calprotectin (<50 µg/g, <100 µg/g, <150 µg/g, <200 µg/g, <250 µg/g	Week 8 and 52Week 16 and 60
Time to outcomes	Time taken to achieve clinical response or remission during induction and maintenance phases	Duration of trial
Maintenance of clinical remission	CDAI <150	Weeks 52 or 60
Sustained clinical remission	CDAI <150	Weeks 52 or 60
Steroid-free clinical remission		Weeks 52 or 60
Safety outcomes	Adverse events	Duration of trial
Scientific outcomes	Comparison of genetic, microbiological, metabolic and immunological factors in the responders with the non-responders	Week 8 and 52Week 16 and 60

BWT, bowel wall thickness; CDAI, Crohn’s Disease Activity Index; CRP, C reactive protein; FMT, faecal microbiota transplantation; IUS, intestinal ultrasound; SES-CD, simplified endoscopic activity score for Crohn's disease.

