### Induction phase

Patients assigned to receive upper gastrointestinal delivery of FMT will undergo endoscopic administration of FMT or placebo into the distal duodenum or jejunum at weeks 0, 2 and 6.

Patients receiving lower gastrointestinal delivery will undergo endoscopic administration of FMT or placebo into the ileum or right colon at week 0, followed by weekly FMT or placebo enemas until week 8.

At the week 8 assessment table 2, patients achieving a clinical response to FMT (CDAI decrease of ≥100 points or CDAI <150) enter the maintenance phase. Patients who achieve a partial response to FMT (CDAI decrease of <100 and >70 points) will be offered open-label extension of FMT for a further 8 weeks; if they fail to achieve complete clinical response to FMT at week 16, they will exit the study. Patients receiving initial (induction) placebo will be offered 8 weeks of open-label induction active FMT therapy; if they fail to achieve complete clinical response to FMT at week 16, they will exit the study. Patients receiving placebo therapy who achieve a clinical response at week 8 will exit the study.

**Table 2 T2:** Clinical outcomes assessments

	Method of assessment	Timepoints
Disease activity	Crohn’s Disease Activity Index	Weeks 0, 2, 6, 8 (±16), 16 (or 24), 24 (or 32), 32 (or 40), 40 (or 48), 48 (or 56), 52 (or 60)
Biomarkers	Blood: C-reactive protein	Weeks 0, 2, 6, 8 (±16), 16 (or 24), 24 (or 32), 32 (or 40), 40 (or 48), 48 (or 56), 52 (or 60)
	Stool: calprotectin	Weeks 0, 2, 8 (±16), 24 (or 32), 52 (or 60)
Sonographic assessment	IUS BWT <3 mm and/or Limberg Score 0 or 1; MRI BWT <4 mm and no/minimal wall enhancement	Weeks −3, 8 (±16), 52 (or 60)
Quality of life measures	Short-IBD-Q and EuroQol (EQ5D)	Weeks −3, 8 (±16), 52 (or 60)
Psychological assessment	Hospital Anxiety and Depression Scale (HADS)	Weeks −3, 8 (±16), 52 (or 60)
Endoscopy assessment	SES-CD	Weeks 0, 8 (±16), 52 (or 60)
Histological assessment	Presence of acute inflammation; Robarts Histology Index	Weeks 0, 8 (±16), 52 (or 60)
Diet tolerability	24-hour diet recall; Diet compliance assessment; Food additive survey	Weeks −3, 0, 8 (±16), 52 (or 60)
Safety	Surveillance	Duration of trial and up to 5 years following withdrawal/exit

BWT, bowel wall thickness; SES-CD, simplified endoscopic activity score for Crohn's disease.

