#### Concomitant Crohn’s disease therapies

Patients will continue stable doses of their prestudy Crohn’s disease therapies, except for rectal therapies, which are not permitted due to the risk of trauma and potential subsequent bacteria translocation. Stable doses for 2 months prior to the study are required for immunomodulators and biologic agents, 1 month for small molecule inhibitors and 2 weeks for aminosalicylates.

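### Maintained and sustained remission are both scored on CDAI below 150 at week 52/60 with no rescue condition, so a retained, rescued relapser counts as a success and can distort the maintenance comparison

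*Protocol article*

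**What the plan says.** All references are to the protocol article.

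- **Endpoints (Primary and secondary endpoints, Table 1).** The rows "Maintenance of clinical remission" and "Sustained clinical remission" have the same definition, CDAI below 150, and the same timepoint, week 52 or 60. Neither mentions rescue treatment.
- **Steroids (Corticosteroid use).** A steroid started after entry is classed as a deviation, with this allowance: "However, patients can remain in the study unless it occurs within 4 weeks of the primary endpoint assessment, or if greater than two courses". Only courses lasting over one month count towards that limit, which runs over the whole study. The primary endpoint is at week 8.
- **Treatment failure (Early discontinuation/withdrawal/treatment failure).** Recurrence counts as failure when it is symptomatic, "necessitating unscheduled endoscopic or surgical intervention or addition of new drug therapy, associated with confirmed active disease". Failed steroid withdrawal is also listed. A dose increase of an existing Crohn's drug is not. The section opens with "Patients may be withdrawn from the study if any of the following occurs", so withdrawal is discretionary, and it does not say how a failure is scored on any endpoint.
- **Background drugs (Concomitant Crohn's disease therapies).** "Patients will continue stable doses of their prestudy" treatments. No consequence is given for changing a dose.
- **Visits (Table 2).** CDAI is scheduled at weeks 16, 24, 32, 40, 48 and 52, or eight weeks later for patients who came through open-label treatment.
- **Analysis (Statistical analysis).** Binary secondary outcomes in both phases are compared between arms with a log-link binomial model. The missing-data strategy is said to depend on the intercurrent event.

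**The concern.** Maintaining remission is one of the two aims in the Objective, and the 1:1 re-randomisation exists to test it. A patient who relapses at week 32, has a steroid course or a biologic dose increase, stays in the study and has CDAI below 150 at week 52 meets both definitions as written. The name of either endpoint suggests the opposite result for that patient. The sustained endpoint adds nothing to the maintained one, because it uses none of the CDAI visits between re-randomisation and the final assessment.

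Rescue follows relapse. If FMT works, relapse should be commoner on placebo, so more placebo patients would be open to being reclassified as successes. What is at stake is how far the estimated maintenance effect can be interpreted. The week-8 primary result is not touched.

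**Working it through.** **1. The plan's own figure.** Inputs from Sample size, Randomisation and stratification, and the Discussion: 60% versus 30% response, two-sided alpha 0.05, 80% power, 2:1 allocation, 20% dropout. With pooled variance and no continuity correction, the pooled rate is (0.30 + 2 × 0.60)/3 = 0.50, and

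placebo n = [1.96 × √(0.25 × 1.5) + 0.8416 × √(0.21 + 0.24/2)]² / 0.30² = 31.5, rounded up to 32.

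That gives 32 + 64 = 96 completers and 96/0.80 = 120 enrolled, as stated. This sizing is for induction and is not in question. The article states no sample size for maintenance.

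**2. Likely size of the maintenance phase.** From 96 completers:
- Week-8 FMT responders: 64 × 0.60 = 38.4.
- Placebo non-responders who may take open-label FMT: 32 × 0.70 = 22.4. Placebo responders leave: "Patients receiving placebo therapy who achieve a clinical response at week 8 will exit the study".
- Assumed open-label response of 30% to 60%: 6.7 to 13.4 further entrants. The 30% is an assumption.
- Total: about 45 to 52, or 38 if no open-label patient enters. FMT partial responders are not counted.
- Per arm: about 19 to 26, so one patient moves an arm's rate by 1/26 = 3.9 to 1/19.2 = 5.2 percentage points.

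**3. Effect of the scoring rule.** Let p be the proportion in an arm in remission at week 52/60 without rescue, and r the share of the remaining patients who are rescued, retained and below 150 at that visit. The Table 1 rule then observes p + r(1 − p), and

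observed difference = (pF − pP) + rF(1 − pF) − rP(1 − pP).

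The article gives neither p nor r for maintenance. The table uses 60% and 30% purely as an illustration; in the article they are expected week-8 response rates. All values of r are assumed.

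| rF | rP | FMT | Placebo | Difference | Risk ratio |
|---|---|---|---|---|---|
| 0 | 0 | 60% | 30% | 30 points | 2.00 |
| 10% | 10% | 64% | 37% | 27 points | 1.73 |
| 20% | 20% | 68% | 44% | 24 points | 1.55 |
| 30% | 30% | 72% | 51% | 21 points | 1.41 |
| 10% | 30% | 64% | 51% | 13 points | 1.25 |
| 20% | 10% | 68% | 37% | 31 points | 1.84 |
| 40% | 10% | 76% | 37% | 39 points | 2.05 |

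With equal shares the difference shrinks by the factor (1 − r). With equal p and equal r in both arms, the difference stays at zero. Under these rates, dilution turns into inflation on the difference scale once rF/rP exceeds 0.70/0.40 = 1.75. On the planned risk-ratio scale the threshold is 2 × 1.75 = 3.5.

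**4. In whole patients.** With 26 per arm and 16 versus 8 truly maintained, the risk ratio is 2.00. Two rescued placebo relapsers make it 16 versus 10, a risk ratio of 1.60.

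**The case against.** **The scoring of rescue may be left to the analysis plan.** An article often omits such detail, and this one mentions intercurrent events. But that sentence concerns missing data, and a rescued patient who attends week 52 has an observed CDAI. An analysis plan would have to add a condition that the stated definitions lack.

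**Much rescue is already treatment failure.** This stands in part. A new drug for confirmed recurrence is a named failure, and a steroid course for such a recurrence plausibly is too. A failure who is withdrawn may have no week-52 CDAI to count. A reader might therefore infer that the plan lets every rescue pass, and the text does not support that. What remains is narrower: failures the investigator keeps in, steroid courses that the corticosteroid section tolerates, and dose escalation. The two sections also pull in different directions on a steroid started for relapse.

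**Other safeguards exist.** Dose changes breach the stable-dose rule, a per-protocol analysis is planned, the limit on steroid courses covers the whole study, and steroid-free remission is a separate endpoint. These help, but none changes the score on the two rows at issue. The steroid-free row addresses steroids only.

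**The comparison has not been shown to be biased.** This stands. A reader might infer that it is biased, or biased against FMT. The article gives no rescue rates. Equal rescue shares only dilute a real effect, which is conservative for FMT, and equal relapse and rescue leave a null comparison unbiased. Unequal shares are possible, for example if patients who have already received FMT recognise a placebo without odourant, but that is conjecture. CDAI below 150 regardless of rescue is also a legitimate measure in itself, though the two endpoint names describe something else.

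**Conclusion.** The point holds as a defect in stated definitions. Following the article's rules, a patient who relapses in maintenance, is rescued, is retained and ends below 150 is scored as both maintained and sustained, and those two endpoints are indistinguishable.

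This can distort the re-randomised maintenance comparison. The direction is dilution if rescue succeeds equally often in both arms, and is open if it does not. The size cannot be derived from the article. The risk ratios of 1.25 to 2.05 against a true 2.00 rest on borrowed rates and assumed rescue shares, and show sensitivity only. With roughly 19 to 26 patients per arm, a few such patients would matter. The endpoints are secondary. The change should be made, but the trial's primary conclusion does not depend on it.

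**What to change.** 1. For the week-52/60 clinical remission endpoints, score as not in remission, in either arm, any patient who after re-randomisation had:
   - a new Crohn's drug;
   - a dose increase or interval shortening of an existing Crohn's drug;
   - a steroid course for Crohn's disease;
   - Crohn's surgery or an unscheduled endoscopic intervention for Crohn's disease; or
   - any other treatment failure under the withdrawal section.
2. Add dose escalation to the treatment-failure definition, and reconcile that section with Corticosteroid use, so that a steroid course started for relapse has one stated status.
3. Define sustained remission as CDAI below 150 at the maintenance visits already in Table 2 as well as at week 52/60. Patients enter maintenance on response, so some may start at 150 or above. State from which visit the count begins.
4. Keep rescued patients in follow-up, and report CDAI below 150 regardless of rescue as a sensitivity analysis.

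The cost is a few lines of protocol and analysis-plan wording, plus dated records of Crohn's drug changes reviewed blind to arm. Remission rates would be somewhat lower in both arms, by an amount that depends on how often rescue occurs. No extra visits are needed, and the clinical decision to rescue is unchanged.
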